### 2.6. Intervention

#### 2.6.1. DCHP Implementation, Hospital Engagement and Ward Delivery

The DCHP includes a whole-of-hospital communication training program for all staff. Other key components are the development of hospital-specific clinical pathways (protocols, policies), executive management support, and ward-based ‘champions’ for the identification and management of CI. The DCHP also requires close engagement with carers/family of patients with CI. The primary vehicle for the program’s hospital engagement is an easily recognizable bedside alert: the ‘Cognitive Impairment Identifier’ (CII—see Figure 1).

The education and training sessions are aimed at enabling staff to better understand, and work with, patients with CI and their carers/family. Initial training of the local teaching staff will be conducted by the DCHP National Implementation Team. It is anticipated that, during implementation, the education program will be delivered to 80% of all staff with patient contact on target wards. Cross-over from Baseline to Intervention will not occur until a minimum of 40% of target staff have received training.

#### 2.6.2. Measures of Successful Implementation and Confounders

Successful adoption of the DCHP will have significant influence on the results of the evaluation. Target ward screening rates will be collected monthly. It is anticipated that 100% of patients aged 65+ will be screened and the CII used for 80% of those who screen positively. Staff education rates will be monitored to ensure a sustained rate of 80% over the 12 months of the program.

#### 2.6.3. Intervention Costs

The resources used in the intervention will be fully costed and attributed to the inpatient population aged 65+ in the relevant wards. This includes the cost of developing the training package, staff training costs (time), and the time taken to conduct screening. The cost of the training package will be treated as a capital cost with an allowance made for periodic updates. Costs attributable to evaluation will not be included in the cost analysis.

#### 2.6.4. Blinding

Blinding will not occur, as there is no practical way to blind hospital staff or members of the evaluation teams.

#### 2.6.5. Sample Size, Power Calculation and Analysis

Based on a conservative estimate of 750 positive screens for CI in each period, the target sample size is a total of 3750 patients. The required sample has been calculated with power 0.8, type I error 0.05 and design effects based on clustering effect (ICC) at site (0.05) level. It is estimated that for a complication rate ranging from 20–26%, this sample size will enable detection of a 22–25.5% or more reduction in risk ratio (RR). This is equivalent to a minimum 5–5.5% reduction in absolute risk. A generalized linear mixed model for a binary outcome with time epoch as a fixed factor and hospitals as a random effect for an incomplete stepped-wedge design with a cross-sectional design was adopted for the power calculation [29]. Stata software was used for this purpose [30].

In relation to the secondary outcomes, based on type I error of 0.05 and a power of 0.9, a target sample size of 160 DemQols per site (80 at baseline and 80 at intervention) is required to detect 15-point differences in health-related quality-of-life score.

Assuming a type I error of 0.05 and a power of 0.8, a target sample size of 140 carer surveys (70 at baseline and 70 at intervention) is required to detect a minimum effect size of 0.4.

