## 2. Materials and Methods

### 2.1. Study Design and Setting

The impact evaluation of the DCHP will use a prospective, stepped-wedge, cross-sectional, continuous-recruitment study design. Patients aged 65+ will be screened for CI within 24 h of hospital admission and included if they have CI. Recruitment will occur continuously over the study period, with individual patients remaining in the study for the length of their hospital stay. Patients aged 65+ admitted to the target wards of a single hospital are referred to as a cluster; there will be four clusters across four Australian jurisdictions. Three sites are large metropolitan hospitals with a university affiliation; and one is a regional hospital. At each hospital, the wards selected to implement the DCHP will be determined by level of interest from the nursing leadership team and a requirement for a spread of wards across medical, surgical, and acute aged care. The Baseline period was determined by the estimated time required to achieve 80% patient screening and 40% staff education. The 42-week intervention period was considered sufficient time for change to be measurable within the constraints of the project funding. Consistent with a stepped-wedge trial design [19], each cluster provides both before and after observations, and clusters incrementally shift from control to intervention (see Table 1—Stepped-Wedge Timeline). Hospital-acquired complications data will be analyzed cross-sectionally.

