### 2.5. Outcome Measures

The primary outcome measure will be the change in the rate of the combined risk of one or more of the following hospital-acquired complications: urinary tract infection, pressure injury, pneumonia or delirium before and after the adoption of the DCHP. The rate of this combined risk will be determined for patients who screen positive for CI over a 12-week period before the introduction of the DCHP, and for patients who screen positive for CI over four consecutive 12-week periods during implementation. A summary of primary and secondary outcomes as well as relevant instruments and sources is provided in Table 3. Falls rates will be a secondary outcome as per Medibank Private methodology, using the Y9222 flag within the ICD code to indicate whether a fall occurred in hospital or not [27].

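### The stated 80% power for a 5–5.5 point reduction does not follow from the stated stepped-wedge inputs; with calendar periods, 3750 patients give about 50–68%

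*Protocol article*

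**What the plan says.** All of this is in the protocol article.

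- Section 2.6.5 sets the size: "Based on a conservative estimate of 750 positive screens for CI in each period, the target sample size is a total of 3750 patients".
- It gives the operating characteristics as "power 0.8, type I error 0.05 and design effects based on clustering effect (ICC) at site (0.05) level".
- The claim is made "for a complication rate ranging from 20–26"%: "this sample size will enable detection of a 22–25.5% or more reduction in risk ratio (RR"). The next sentence adds: "This is equivalent to a minimum 5–5.5% reduction in absolute risk".
- The model behind the calculation has "time epoch as a fixed factor and hospitals as a random effect for an incomplete stepped-wedge design".
- Section 2.1 fixes the number of clusters: "there will be four clusters across four Australian jurisdictions".
- Section 2.5 measures the primary outcome "over a 12-week period before the introduction of the DCHP, and for patients who screen positive for CI over four consecutive 12-week periods during implementation". One control and four intervention periods account for 5 x 750 = 3750.
- Table 1 gives the stagger. T1 begins in December 2015, March 2016, May 2016 and July 2016 for hospitals 1 to 4.

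The article does not state the sidedness of the test, which Table 1 cells count as control, or whether an epoch is a calendar column or a period counted from each hospital's own start.

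**The concern.** In a stepped wedge with a fixed effect for each period, the intervention effect is learned mainly from calendar periods in which some hospitals are still control and others have crossed over. With one control window and four intervention windows per hospital placed on Table 1, the 20 cells spread over eight calendar columns (September 2015 to February 2017). Only December 2015, March 2016 and May 2016 contain both kinds of hospital. So thin an overlap, with four clusters, makes 80% power at 5–5.5 points doubtful.

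This is the primary outcome. If true power is well below 80%, a null result read against the printed figure would look like stronger evidence against the program than it is.

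**Working it through.** **Inputs from the article:** 3750 patients, 4 hospitals, 5 periods each, ICC 0.05, alpha 0.05, control rates 20% and 26%.

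**Assumptions:** equal split, 3750 / 20 = 187.5 per hospital-period; two-sided test (one-sided also shown); one random intercept per hospital.

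**Effects claimed.** Relative: 25.5% x 20 = 5.1 points (20% to 14.9%) and 22% x 26 = 5.72 points (26% to 20.28%). Absolute: 5 points (20% to 15%) and 5.5 points (26% to 20.5%). The two statements differ slightly at the upper end (5.5 / 26 = 21.2%, not 22%), so I tested all four.

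**Model.** Cell means with fixed calendar columns and a random hospital intercept. s² = p(1−p), cell variance σ² = s²/187.5, between-hospital variance τ² = s² x 0.05/0.95. Power = Φ(d/SE − 1.96). Detectable difference at 80% = (1.96 + 0.84) x SE = 2.80 x SE.

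**Complete 4 x 5 layout, checkable by hand** (Table 1 columns September 2015 to July 2016, with BL1 and BL2 as control). The closed form is

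Var = Iσ²(σ² + Tτ²) / [(IU − W)σ² + (U² + ITU − TW − IV)τ²]

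with I = 4, T = 5, U = 10 intervention cells, W = 0+1+4+9+16 = 30 (squared column totals) and V = 16+9+4+1 = 30 (squared row totals). The bracket is 10σ² + 30τ². At p = 0.20, σ² = 0.16/187.5 = 0.000853 and τ² = 0.00842. Then Var = 4 x 0.000853 x 0.04296 / (0.00853 + 0.25263) = 0.000561, so SE = 0.0237 and the detectable difference is 6.6 points.

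**Staircase layout** (last BL2 plus T1–T4 per hospital). The same model by generalised least squares on the 20 cells gives SE 0.0255 at p = 0.20, so 2.80 x 0.0255 = 7.1 points. At p = 0.26, SE is 0.0280, or 7.8 points.

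The ranges below run from variance at the control rate to variance at the intervention rate:

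| Change | Staircase SE | Two-sided power | 4 x 5 SE | Two-sided power |
|---|---|---|---|---|
| 20% to 15% | 0.0255–0.0228 | 50–59% | 0.0237–0.0212 | 56–66% |
| 20% to 14.9% | 0.0255–0.0227 | 51.5–61% | 0.0237–0.0211 | 58–68% |
| 26% to 20.5% | 0.0280–0.0258 | 50–57% | 0.0260–0.0239 | 56–63% |
| 26% to 20.28% | 0.0280–0.0257 | 53–61% | 0.0260–0.0238 | 59–67% |

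- Detectable difference at 80%, two-sided: 6.4–7.8 points (staircase), 5.9–7.3 points (4 x 5).
- One-sided power: 62–73% (staircase), 68–78% (4 x 5).
- Logistic simulation of the relative effects, with hospital and column fixed: about 54% (staircase) and 62% (4 x 5).
- ICC between 0.01 and 0.10 moves staircase power only over 53–56% (absolute effects, mean-rate variance).

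**Epoch counted from each hospital's start.** The intervention indicator equals the sum of the T1–T4 indicators, so a separate intervention term is aliased with epoch. The before/after contrast itself is estimable. Hospital effects cancel, and pooling T1–T4 for 20% to 15% gives SE = √(0.16/750 + 0.1275/3000) = 0.0160, d/SE = 3.13, power 88%. Across the four effects and the variance choices the range is about 87–94%.

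**What comes close to the stated figure.** With ICC set to 0 in the 4 x 5 layout, SE = √(0.4σ²). At the mean rate 17.5%, σ² = 0.144375/187.5 = 0.00077 and SE = 0.0175, which gives power 81% and a detectable difference of 4.9 points; at 26% it is 5.5 points. That matches the printed figures but drops the stated ICC.

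**The case against.** The strongest defence is that Section 2.5 defines the outcome on periods counted from each hospital's start, where the before/after contrast is estimable. Baseline against a single intervention period (750 v 750) has about 71–77% two-sided and 81–85% one-sided power, and its one-sided detectable difference of about 4.8–5.4 points is near the printed one. This stands as a possible origin of the number. But that contrast uses 1500 of the 3750 patients, needs a one-sided test that is not stated, and takes no account of calendar time. The pooled contrast, which uses everyone, overshoots 80%.

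A reader might infer four stronger things, and the article supports none of them:

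- *That 51–61% is the true power.* This is one layout under assumptions on sidedness, site split and control cells. The word incomplete in Section 2.6.5 favours the staircase over the 4 x 5 layout but does not identify its cells.
- *That the effect cannot be estimated with site-relative epochs.* Only a separate intervention term is lost.
- *That the trial has near-even odds of missing its target effect.* The article calls 750 per period conservative, so recruitment may exceed it (Section 4 admits it may also fall short). The model is given for the power calculation, and the final analysis model may be set elsewhere.
- *That the BL1 columns would restore the power.* Section 2.1 ties the baseline length to the time needed to reach 80% screening. BL1 may therefore hold few or selectively obtained screens, and a positive screen is the entry criterion.

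The mismatch between relative and absolute effects (5.1–5.7 against 5–5.5 points) is minor.

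**Conclusion.** The concern holds. With calendar period fixed, hospital random, ICC 0.05 and 3750 patients, two-sided power at the stated effects is about 50–61% in the layout that follows Section 2.5 and Table 1, and at most about 68% in the most favourable layout examined. One-sided testing raises the ceiling to about 78%. The detectable difference at 80% power is about 6–8 points, not 5–5.5. With site-relative epochs the pooled contrast has about 87–94%, at the price of leaving calendar time unadjusted, which is what the Discussion expects the design to control.

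The conclusion rests on an equal split and a single random intercept. A hospital-by-period variance would lower power further, and normal-theory power with four clusters is already optimistic. The article cannot show how 80% was obtained.

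**What to change.** In Section 2.6.5:

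1. Define epoch as the Table 1 calendar column.
2. State which cells count as control and whether the test is one- or two-sided.
3. Re-run the power program on exactly that layout.
4. Print the resulting power at the stated effect (expect about 50–68% two-sided) or the difference detectable at 80% (expect about 6–8 points).
5. Derive the absolute figures from the relative ones so that they agree at both control rates.
6. Claim no power from BL1 columns unless CI screening in those periods is shown to be adequate.

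The cost is one re-run and a reworded paragraph. Recruitment need not change, but the advertised detectable effect becomes less favourable.

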## 3. Discussion

A stepped-wedge design is a logical fit, given that hospitals are constantly changing their care models in different ways and across varying time courses. The stepped-wedge methodology is designed to control for potential bias that occurs as a result of variations in hospital practice and the introduction of new regulations. In addition, while the value of the program has been accepted by the funding body and participating sites on the basis of previous rollouts and grey literature reports [9,18], this study is expected to provide a platform for adoption of the DCHP across each State in Australia. Such an outcome requires robust evidence of clinical benefit and cost effectiveness, particularly as Australia is a federated democracy where acute hospital care is the responsibility of individual States.

The order of implementation is not randomized. While randomization would be preferable, with only four sites this is not critical. In addition, introducing significant change in hospitals requires hospital ownership of the program, which is facilitated by a negotiated start date reflecting organizational readiness.

This evaluation will measure the hospital-acquired complication rate in a large prospective cohort of older Australian hospital patients with and without CI. The international literature on hospital-acquired complication rates in patients with dementia has been based on retrospective data [31], which is known to be incomplete and potentially missing half the at-risk group [3]. New international studies are prospective but smaller in terms of sample sizes [32]. Real-time capture of data on all older patients with CI in hospital may have the effect of either decreasing or increasing the recorded hospital-acquired complication rate. We hypothesize that patients with mild symptoms, who are possibly missed in retrospective studies, are at greater risk because they receive no or little support beyond that given for their documented comorbidities. Therefore the risk rate will be higher. It is possible that this assumption is incorrect and the complications are rather a reflection of the degree of CI, resulting in a reduced complication rate reflecting milder CI.

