## 4. Limitations

The CI screening tools will not be consistent across all sites. It is possible, therefore, that the population identified as at risk of hospital-acquired complications will vary across participating hospitals. This variation will be mitigated by pooling the results across all four sites. The sensitivity and specificity values of the screening tools used at the four sites are similar (AMT4 ; sensitivity 80% and specificity 76% [33]; AMTS; sensitivity 81% specificity 84% [34]; MiniCog; sensitivity 76% and specificity 73% [35]). The Clock Drawing Test [23] was used in addition to some screening tools as it has previously been found to increase the sensitivity and specificity of other screening tests [36]. As there are a wide variety of CI screening tools used in Australia, the variance in tool use reflects real practice.

Equally, while there is relative consistency of data extraction methodology, in Australia there is variance in how hospital events are recorded. This may also impact on the final data.

The target number of positive screens for CI was estimated from national data and experience from previous rollouts of the DCHP in Victoria. If the number of positive screens is significantly fewer than the predicted number, this could impact on the statistical power of the study.

While there were no exclusions within the target recruitment population, it is likely that universal screening of all patients 65+ in a hospital environment will not be achieved. The results will be reported on an intention-to-treat basis. This is a conservative approach but is likely to reflect real-world practice, so a positive result is more likely to translate across hospitals.

The DEMQoL [25,26] was not originally designed for use in the hospital setting. It is expected that there may be a significant number of patients who may not be able to complete the survey because of ill-health.

The National Commission on Safety and Quality in Health Care has released advice relating to screening for CI in acute care, and the screening for, and management of, delirium (ACSQHC 2013). As this advice will be taken up at the state level gradually, there may be some impact on screening practice that is not attributable to implementation of the DCHP which should be mitigated by the study design.

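### The only stated model treats hospital as random although start order was negotiated; carried into the primary analysis with calendar periods, it would let stable hospital differences bias the programme effect in either direction

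*Protocol article*

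**What the plan says.** Section 2.6.5, whose heading covers sample size, power and analysis, describes a "generalized linear mixed model for a binary outcome with time epoch as a fixed factor and hospitals as a random effect" for an incomplete, cross-sectional stepped wedge. The sentence ends by saying that this model "was adopted for the power calculation". No other model appears in the article. Section 2.1 adds only that complications are analysed cross-sectionally, and section 4 that results are reported by intention to treat.

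On order of start, the Discussion says: "The order of implementation is not randomized. While randomization would be preferable, with only four sites this is not critical". It explains that hospital ownership is helped by a "negotiated start date reflecting organizational readiness".

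On differences between hospitals, section 2.1 describes three metropolitan sites and one regional site. Table 2 assigns different screening tools to different sites. Section 4 accepts that the screened populations may therefore differ and says: "This variation will be mitigated by pooling the results across all four sites".

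**The concern.** A random hospital intercept gives an unbiased programme effect only if a hospital's underlying complication rate is unrelated to when it starts. Randomising the order would secure this in expectation; here the order was negotiated. With calendar period in the model, the estimator combines two sources of information: each hospital's own change at crossover, and a comparison of levels between hospitals already exposed and hospitals not yet exposed in the same period. The second source is contaminated if early and late starters differ in level. The smaller the estimated hospital variance, the more weight it gets, and with four hospitals that variance is often estimated as zero.

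Having only four sites does not make non-random order harmless, because four hospitals are too few for chance to balance their levels. Pooling does not remove level differences either; conditioning on hospital does. What is at stake is the size, and possibly the sign, of the primary effect.

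**Working it through.** **The plan's own figures.** 5 periods × 750 = 3750, as stated. 20% × 25.5% = 5.1 points and 26% × 22% = 5.7 points, close to the stated 5 to 5.5. The stated power of 0.8 was not reproduced with 3750 patients and time as a fixed factor (0.58 to 0.59 two-sided on the layout below, 0.64 to 0.65 on a standard 4 × 5 wedge). The layout used is not stated. That is a separate matter and the point here does not depend on it.

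**Inputs.**
- Layout from Table 1: last training (BL2) column plus T1 to T4 for each hospital, with calendar columns as periods (20 hospital-periods).
- 3750/20 = 187.5 patients per hospital-period; equal hospital sizes are an assumption.
- ICC 0.05 (2.6.5). At a mid-range rate of 23%, hospital SD = √(0.05 × 0.23 × 0.77) = 0.094, or 9.4 points.
- No programme effect and no time trend.

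**Step 1: leakage with the variance known.** In generalised least squares the programme estimate is a weighted sum of hospital-period rates. Adding up the weights within a hospital shows how much of its stable level enters the estimate. At ICC 0.05 the sums for hospitals 1 to 4 in start order are +0.026, +0.004, −0.010 and −0.020. Evenly spaced levels with SD 9.4 points are −10.9, −3.6, +3.6 and +10.9, so

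bias = 0.0256(−10.9) + 0.0038(−3.6) − 0.0096(3.6) − 0.0198(10.9) ≈ −0.55 points.

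The standard error is 2.62 points, so this is about 0.2 SE and a tenth of the target. Over other layouts it ranges from 0.23 to 0.81 points.

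**Step 2: why smaller differences are worse.** If the hospital variance is estimated as zero, the same formula gives sums of +0.565, +0.043, −0.217 and −0.391. With assumed rates of 20, 22, 24 and 26% in start order, bias = 11.30 + 0.96 − 5.22 − 10.17 ≈ −3.1 points. Actual behaviour is a mixture of this and the well-behaved case.

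**Step 3: variance estimated.** Simulation with 4,000 runs per setting, a linear model on hospital-period rates, and risk rising evenly with start order. False benefit is nominally 2.5%.

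| Hospital SD (points) | REML bias | REML false benefit | ML bias | ML false benefit | Variance estimated as zero (REML / ML) |
|---|---|---|---|---|---|
| 2 | −1.5 | 13.0% | −2.0 | 16.6% | 37% / 69% |
| 3 | −1.7 | 15.1% | −2.4 | 23.8% | 19% / 47% |
| 4 | −1.5 | 13.6% | −2.3 | 23.1% | 7% / 23% |
| 6 | −1.0 | 7.9% | −1.5 | 12.1% | 0% / 1% |
| 9.4 (ICC 0.05) | −0.7 | 4.9% | −0.9 | 5.9% | 0% / 0% |

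Hospital as a fixed effect gives bias within 0.05 point and false benefit of 2.5 to 3.0% in every row. Reversing the order gives the same bias towards harm. A logistic random-intercept model fitted by ML to rates of 20/22/24/26% gives −2.2 points and 19%, so the linear approximation is not what produces the result.

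**Step 4: sensitivity.** Adding all BL1 periods lowers the ML maximum to 1.5 points and 14%. Using the last BL1 column in place of BL2 raises it to 3.5 points and 29%. With rates of 20/22/24/26% in all 24 possible start orders, the absolute bias exceeds 1 point in 11 orders (ML) or 7 (REML), and averages 1.0 or 0.7 points.

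**The case against.** The strongest reply is that the sentence describes a power calculation. A reader might infer that the article commits the primary analysis to a random hospital effect; it does not say so. The outcome model may be fixed in a full protocol or analysis plan that is not shown, and its absence from an article is no fault. This stands, and it makes the point conditional. What remains is that the only stated model, read alongside two reassurances that are unsound for it, points the analysis in that direction.

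A reader might also infer that a false benefit is likely, or that the false-positive risk is about 20%. The documents do not support this. At the planned ICC the excess is small. The larger figures need hospital SDs of about 2 to 4 points, which correspond to ICCs of about 0.002 to 0.009 (0.02²/0.1771 to 0.04²/0.1771), well below the planned 0.05. The 20 to 26% in section 2.6.5 is a range of rates considered for power, not a spread between hospitals. Nothing links readiness to complication risk, the regional hospital's place in the order is not given, sites 2 and 3 share screening tools, and section 4 describes the tools' accuracy as similar. A masked benefit is as possible as a false one.

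The leak also depends on reading time epoch as calendar period. Section 2.5 defines periods relative to each hospital's own start. Under that reading the leak vanishes, but programme effect and epoch can no longer be separated. The reference to an incomplete stepped wedge favours calendar periods without settling the matter.

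Finally, a random intercept is a recognised stepped-wedge model, and fixed effects narrow the inference, whereas the Discussion hopes for adoption in every State. That is a real cost, but four hospitals with negotiated start dates give little basis for wider inference under either model.

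**Conclusion.** The point holds conditionally and is worth correcting; it should be fixed but does not by itself invalidate the plan. If a random hospital effect with calendar periods becomes the primary analysis, stable hospital differences aligned with start order bias the result in an unknown direction. The size is about 0.5 to 1 point with about 5 to 6% false benefit near the planned ICC, and about 1.5 to 2.4 points with 13 to 24% if hospital SDs are about 2 to 4 points. Both ranges assume perfect ordering by start date, equal hospital sizes, the Table 1 layout used above and a two-sided 5% test. The planning ICC is no safeguard, because the problem grows when the true differences are smaller than planned. Four hospitals cannot show that level and start order are unrelated, but the choice of model can make the question irrelevant for stable differences.

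**What to change.** - In 2.6.5, state that the primary outcome model has hospital as a fixed effect (three indicator terms) and calendar period as a fixed factor. Base the power calculation on the same model, and keep the random-effect model as a sensitivity analysis.
- In the Discussion, replace the claim "While randomization would be preferable, with only four sites this is not critical", and in section 4 replace "This variation will be mitigated by pooling the results across all four sites". Say instead that fixed hospital effects remove stable differences between hospitals, including those due to screening tool, but not hospital-specific time trends.

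Cost: a line of model wording and two sentences. At ICC 0.05 and a 23% rate the standard error goes from 2.62 to 2.70 points (about 3%), or to 2.64 (about 1%) if the between-hospital share is taken out of the residual variance. On the layout above, for 5.1 points from a 20% rate, the SE goes from 2.36 to 2.44 and two-sided power from Φ(5.1/2.36 − 1.96) = 0.58 to Φ(5.1/2.44 − 1.96) = 0.55. Inference is formally limited to these four hospitals.

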### 2.4. Data

Hospital-acquired complication data will be drawn from routinely collected hospital data sets and submitted to the Health Roundtable (HRT) [24], which is a not-for-profit membership organization of participating hospitals across Australia and New Zealand. HRT holds routinely collected data for 8 years for all the hospitals in the DCHP. The hospital-acquired complications for the evaluation were derived from hospital-coded patient records. This method is based on work by Needleman et al. [12], and updated to ICD10 by Bail et al. [2]. All the diagnostic codes for the patients’ episodes will be examined separately. Patients with at least one of four complications will be recorded as positive for a hospital-acquired complication.

Staff surveys, carer surveys and patient DemQoLs [25,26] will be collected during the pre-intervention period and at approximately six months post-intervention.

Ethics approval has been obtained for data sharing with the external evaluation team. Patient data, which will be de-identified prior to analysis, will include patient descriptors (e.g., age, name, Unit Record Number (UR), Aboriginal and Torres Strait Islander (ATSI) status, comorbidity index), and episode descriptors (e.g., length of stay, discharge ward).

Data will be stored on a secure server with restricted access. Data will be entered into Excel spreadsheets on-site and at the DCHP National Office for later analysis using the SPSS and Stata statistical software packages. To ensure data integrity, all data cleaning and data entry will be completed by two research assistants using a cross-check methodology. Responsibility for appropriate and secure data storage rests with the primary investigator and the evaluation team.

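### The carer survey target of 70 + 70 gives about 65% power, not the stated 80%, for an effect size of 0.4

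*Protocol article*

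**What the plan says.** Protocol article, section 2.6.5, last paragraph, opens with the operating characteristics, "Assuming a type I error of 0.05 and a power of 0.8", and then gives the target: "a target sample size of 140 carer surveys (70 at baseline and 70 at intervention) is required to detect a minimum effect size of 0.4". It does not state sidedness, the test, the standard deviation, or any allowance for clustering or incomplete surveys.

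The paragraph before it sets the DemQol target explicitly for each site. The carer sentence has the same structure but carries no such qualifier, so as printed 140 is the study total.

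On timing, section 2.4 says of the staff, carer and patient surveys that they "will be collected during the pre-intervention period and at approximately six months post-intervention". Section 2.1 describes a cross-sectional design with continuous recruitment, "with individual patients remaining in the study for the length of their hospital stay". Table 3 lists carer satisfaction as a secondary outcome. The Discussion (section 3) also relies on it as one of the markers of how well each hospital has taken up the program.

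**The concern.** The sentence fixes all four quantities of a simple power calculation (alpha, power, sample size and effect size), so it can be checked without the full protocol or an analysis plan. The familiar benchmark for an effect size of 0.4 at 80% power is about 100 per group. A figure of 70 is well short of that.

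Two things are at stake. The number is the collection target, so an error in it decides how many surveys are gathered. It also governs how a null result is read: anyone who believes the comparison had 80% power for 0.4 SD will take a non-significant result as stronger evidence against a carer benefit, or of poor program adoption, than it is.

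**Working it through.** **Inputs**
- Type I error 0.05 and power 0.80 (section 2.6.5). Sidedness is not given; two-sided is taken as the convention and one-sided is also tried.
- n = 70 per period, 140 in all (section 2.6.5).
- Effect size d = 0.4, read as a standardised mean difference (assumption; the text does not define it).
- Independent samples. Patients are in the study only for their stay (section 2.1), the two survey waves are months apart (section 2.4), and no pairing is described.

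**Trying to reproduce 70 per period**

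n per group = 2 (z₁₋α/₂ + z₁₋β)² / d²

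- Two-sided: 2 × (1.960 + 0.842)² / 0.4² = 2 × 7.849 / 0.16 = 98.1, so 99. The t-test gives 99.1, so 100 per period and 200 in all.
- One-sided: 2 × (1.645 + 0.842)² / 0.16 = 77.3, so 78. The t-test gives 77.97, also 78.

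Neither gives 70.

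**Power at 70 per period**

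Power ≈ Φ(d√(n/2) − z), with d√(n/2) = 0.4 × √35 = 2.366

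- Two-sided: Φ(2.366 − 1.960) = Φ(0.406) = 65.8%; t-test 65.2%.
- One-sided: Φ(2.366 − 1.645) = Φ(0.721) = 76.5%; t-test 76.1%.

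**Effect detectable with 80% power at 70 per period**
- Two-sided: 2.802 × √(2/70) = 0.474; t-test 0.477.
- One-sided: t-test 0.422.

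**Other readings**

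| Reading | Result |
|---|---|
| Paired t-test, standardised change 0.4 | 51.01, so 52 pairs; 70 pairs give 91% power |
| Cohen's f = 0.4, two groups | about 52 in total |
| Wilcoxon test, normal data | 99 ÷ (3/π) ≈ 104 per period |
| 10% incomplete surveys on top of 99 | 99/0.9 = 110 per period |
| 70 + 70 at each of 4 sites, pooled (280 per period, 560 in all) | power 99.7%; detectable effect 2.802 × √(2/280) = 0.24 |

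None of these gives 70 + 70 at 80% power for 0.4.

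**Clustering by hospital.** The effect depends on the analysis, so a range is shown. All of it is assumption, because the article gives no ICC for the carer survey.
- If a constant site effect is removed by comparing periods within hospitals, and sites are balanced, an ICC of 0.05 shrinks the residual SD to √0.95. Then d = 0.4/√0.95 = 0.410 and power is Φ(0.410 × 5.916 − 1.960) = Φ(0.468) = 68%.
- If nothing is gained from within-site comparison, 140/4 = 35 surveys per site give a design effect of 1 + 34 × ICC. That is 1.34 at ICC 0.01 (power 53%) and 2.70 at ICC 0.05 (power 30%).
- For 70 per period to suffice, the correlation would have to satisfy 98.1 × (1 − ρ) = 70, so ρ ≈ 0.29. The only ICC in the article, for the primary outcome, is 0.05.

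**The case against.** The best rescue is a one-sided test with n fixed at 70. The detectable effect is then 0.42, which could have been printed as 0.4. This is possible, but the text does not mention a one-sided test and calls 0.4 the minimum effect. Even if it is granted, power at 0.4 is 76%.

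Second, the effect size may not be standardised. If 0.4 were a raw difference on the survey scale, an SD of about 0.4/0.477 = 0.84 would make 70 + 70 correct. The survey itself is in supplementary material that is not at hand, so this cannot be excluded. However, no SD is given, and the term without units ordinarily means a standardised difference.

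Third, a per-site qualifier may have been lost when the protocol was condensed, given the neighbouring DemQol sentence. The pooled comparison would then be amply powered. The sentence would still be wrong, because the total would be 560 and the matching detectable effect about 0.24. And if the intent were a separate comparison within each hospital, power there would again be 65%.

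Fourth, nothing says in so many words that the two waves are different carers. That is inferred from the stay-only, cross-sectional design. The inference is sound, and a paired reading at d = 0.4 would need 52 pairs, so it does not explain 70.

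What stands is that the cause of the error is unknown, and that figures such as 0.48 and 0.24 ignore clustering. Neither point restores the stated 80%.

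**Conclusion.** The statement is wrong as written. For two independent samples, a standardised difference of 0.4 and a two-sided 0.05 level, 140 surveys give about 65% power. The requirement for 80% is about 200, so the target falls short by about 60 surveys (30%). The chance of missing a true 0.4 SD difference is about 35%, against the 20% claimed. With a one-sided test the shortfall is smaller (76% power, 78 per period needed) but remains.

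The conclusion rests on reading the effect size as a mean difference in SD units, on unpaired carers, and on 140 being the study total. The consequence is limited to the carer satisfaction comparison and to what is inferred from it about program adoption. Sample size and power for the primary outcome are a separate calculation and are not touched.

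**What to change.** First state the test, its sidedness, what the effect size is measured in, and whether the target is a total or per site. Then choose the wording that matches:

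- **Keep 140 in total:** say that 70 + 70 surveys give 80% power for an effect size of about 0.48 (about 65% for 0.4), two-sided, before any allowance for clustering.
- **Keep 0.4 at 80% power:** raise the target to about 100 per period (200 in all), again before clustering or incomplete surveys.
- **If 70 + 70 per site was meant:** write 560 surveys in total, with a pooled detectable effect of about 0.24 before clustering.

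If the analysis will account for hospital, add the ICC assumed for the survey score and the resulting figure.

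The first and third options cost one corrected sentence; the first also makes the stated detectable effect somewhat less favourable. The second costs about 60 more surveys and is open only while both periods can still be surveyed.
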